## Abstract

**Introduction:**

Hedonic eating, reward-driven eating rather than out of biological needs, has been proposed as one of the important causes of overweight and obesity in recent years. Dopamine, endocannabinoids, opioids, and ghrelin are among the physiological factors associated with hedonic eating. Since the results of some previous animal studies have indicated the effectiveness of melatonin supplementation on the levels of endocannabinoids, and ghrelin, therefore this pilot study will investigate the effect of melatonin supplementation on plasma levels of endocannabinoid 2-arachidonylglycerol, ghrelin, and the intensity of hedonic eating in overweight/obese females.

**Methods:**

In a randomized, double-blinded, placebo-controlled study, forty-six women with overweight/obesity and high hedonic eating intensity (total score of power of food scale > 2.5) will be recruited. They will receive either a 5 mg/day melatonin supplement (n = 23) or a placebo (n = 23) for 8 weeks. The primary outcomes, including the plasma levels of 2-arachidonylglycerol and ghrelin, and the intensity of hedonic eating will be assessed at the baseline and end of the study. Additionally, the secondary outcomes (dietary intake, and body weight) will be evaluated at the study’s onset, after four weeks, and upon completion of the intervention. A one-way analysis of covariance (ANCOVA) will be used to detect the effect of melatonin supplementation on outcome variables.

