### Blinding

The present pilot study is designed as a double-blind trial, ensuring that neither the researchers conducting the study nor the participants will know which group they have been assigned to. To maintain the double-blind nature, the packages containing melatonin and placebo tablets will be coded as ‘A’ and ‘B’ at the start of the study by an individual not involved in the research process. This coding serves to blind the researchers. Furthermore, the supplement and placebo pills will be made identical in color, shape, smell, and appearance to blind the participants.

Labels on the supplement packs will stay hidden until the study is finished. However, if any adverse events occur, unblinding is allowed according to the Medical Ethics Committee’s guidelines to determine whether the patient received melatonin or a placebo. If dropout rates reach 15% or higher due to adverse effects, we will conduct an intention-to-treat (ITT) analysis.

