### Intervention

Forty-six eligible women will be randomly assigned to either the melatonin group or the placebo group, with 23 participants in each group. Participants will take a 5 mg tablet one hour before bedtime with sufficient water and will be followed up for 8 weeks. The Tehran Darou Pharma & Food Supplement Company will supply the melatonin and placebo tablets, which will be identical in weight, size, shape, taste, color, odor, and packaging. Patients will receive the tablets during monthly study visits, with a total of three visits scheduled for the trial (before the intervention, after 1 month of intervention, and at the end of the intervention). Patients will be instructed on how to use their tablets and will receive weekly follow-up calls to improve response rates and fewer dropouts.

To enhance participant retention, the potential health benefits of melatonin will be explained, and the principal investigator will keep in regular contact with participants via phone calls.

Compliance will be assessed based on the number of unused tablets returned by each participant at the end of week four and the end of the trial. The remaining tablets will be counted to determine the total intake of the tablets. The total intake of tablets for each subject is calculated by subtracting the number of tablets unused from the number of tablets dispensed.

Participants can choose to leave the study at any point. Furthermore, the investigator has the authority to remove subjects from the study if they do not adhere to the protocol. Additionally, patients will be monitored for any adverse events following melatonin consumption. If any adverse events are attributed to melatonin, participants will be advised to discontinue the supplements and will be promptly referred to a specialist for further treatment.

It is important to note that no specific physical activity program, dietary recommendations, or regimens will be provided to the study subjects. Additionally, after considering the eligibility criteria, if subjects are being treated for any kind of disease during the study, they will not be deprived of routine treatment. Participants will receive either melatonin supplements or a placebo alongside their standard treatments.

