### Study outcomes

The primary outcomes of the current trial are to reduce plasma levels of 2-AG, ghrelin, and the scores associated with hedonic eating. The secondary outcomes focus on dietary intake and body weight. Additionally, at the study’s outset, participants will provide their medical history and demographic information, including age, gender, educational background, and marital status.

The intensity of hedonic eating in the first phase of the project and at the end of the study will be measured using the PFS questionnaire, which has been previously validated for the Iranian population [28]. The questionnaire comprises 15 items across three subscales: the “Food Available (FA)” subscale evaluates public thoughts about foods, the “Food Present (FP)” subscale assesses attraction to directly available food, and the “Food Tasted (FT)” subscale evaluates attraction to foods that have a favorable/ preferred taste. The likert scale will be used for scoring, ranging from 1 to 5, where a higher score indicates greater hedonic hunger [32].

Plasma levels of 2-arachidonoylglycerol and acylated ghrelin will be measured before and after the study. For biochemical analysis, A 5 cc blood sample will be collected from each participant after a 10–12 hour fast for biochemical analyses. The blood will be placed in EDTA-coated tubes, centrifuged at 3000 rpm at 4 °C for 10 minutes, and then it will be stored at -80 °C to determine the plasma levels of 2-AG and acylated ghrelin. ELISA kits provided by ZellBio GmbH, [name], Germany, will be used to assess the plasma concentrations of 2-AG and acylated ghrelin.

For the evaluation of dietary intake, including total energy and macronutrient intake, participants will complete three 24-hour dietary recalls. This will include one weekend day and two weekdays, using a validated tool for dietary assessment. These recalls will be conducted through in person or phone interviews at the beginning of the study, after four weeks, and upon the completion of the intervention The Nutritionist IV software will be utilized to process and analyze the dietary information.

Body weight measurements will be taken using a Seca scale, accurate to 0.1 kg, at three key points: at the beginning of the study, after four weeks, and at the end of trial. During these measurements, participants will be wearing in light clothing.

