### Statistical analysis

Data will be analyzed statistically using SPSS 26.0 software, considering P values below 0.05 as indicative of statistical significance. The normality of data distribution will be checked using the Kolmogorov-Smirnov test, and an appropriate method will be applied to normalize variables that do not follow a normal distribution. Mean (standard deviation) and frequency (percentage) will be used to represent quantitative and qualitative variables, respectively. Independent sample t-tests will be used to evaluate differences in baseline means, while paired-sample t-tests will compare within-group differences. For variables assessed three times during the study (at the start, in the fourth week, and in the eighth week), a repeated measures ANOVA will be utilized. Additionally, Analysis of Covariance (ANCOVA) will assess the effects of the intervention between groups, adjusting for confounders such as baseline data and physical activity. In cases where dropout rates of 15% or more, an intention-to-treat (ITT) analysis will be performed. Missing data will be handled using multiple imputation methods.

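### The PFS, a 15-item primary outcome, is not collected at the existing one-month visit, so the imputation has no on-treatment PFS for women who leave before week 8

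*Protocol article*

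**What the plan says.** The three primary outcomes are plasma 2-AG, plasma ghrelin and the PFS score.

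- **Timing of the PFS.** The Abstract (Methods) states that "the intensity of hedonic eating will be assessed at the baseline and end of the study". Study outcomes is more specific about the first measurement: "The intensity of hedonic eating in the first phase of the project and at the end of the study will be measured". The two agree if the screening score serves as the baseline.
- **Timing of the plasma markers.** Study outcomes: "Plasma levels of 2-arachidonoylglycerol and acylated ghrelin will be measured before and after the study".
- **Visits.** The Intervention section describes monthly visits for tablet dispensing: "with a total of three visits scheduled for the trial (before the intervention, after 1 month of intervention, and at the end of the intervention". Unused tablets are counted at week 4 (Intervention), and body weight and dietary recalls are also taken at four weeks (Study outcomes). Participants receive weekly follow-up calls throughout.
- **Attrition and missing data.** Sample size raises 40 participants to 46 for 15% attrition. Statistical analysis says: "Missing data will be handled using multiple imputation methods".

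**The concern.** The plan expects to lose some women and intends to impute their missing values. With a single post-baseline measurement, a woman who leaves before week 8 has no follow-up PFS. Her imputed score then depends on the assumption that leaving is unrelated to the missing PFS once the screening score, arm and other recorded variables are taken into account. An on-treatment score would make that assumption easier to defend.

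The screening score may also be a limited predictor. It is taken in a recruitment phase planned to run from January to October 2024 (Trial status), and the gap to randomisation is not stated. Entry requires a total PFS above 2.5 (Inclusion and exclusion criteria), which narrows its range and invites regression to the mean. How much either feature matters cannot be judged from the document.

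At stake are the credibility of the PFS imputation and a modest amount of precision. The one-month visit already collects two secondary outcomes, and the PFS is the primary outcome that could be added there without a blood sample.

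**Working it through.** **Inputs from the protocol.** Planned n = 40, attrition 15%, enrolled n = 46, 23 per arm (Sample size). Assessment times are as set out above.

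**Assumed input.** r is the correlation between week-4 and week-8 PFS given the baseline covariates. The document gives no value, so the range 0.5 to 0.8 is used, with R² = r².

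**Step 1: the plan's own figure.** 40 × 1.15 = 46, which reproduces the stated total. Dividing by the retained fraction gives 40 / 0.85 = 47.06, or 48 with equal arms. The difference is small and is not the point here.

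**Step 2: expected losses.** 46 × 0.15 = 6.9, about 7 women or 3 to 4 per arm. Women with a week-8 primary value: 46 × 0.85 = 39.1.

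**Step 3: what the imputation can use for those 7 women.**

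| Available under the current plan | Not available |
|---|---|
| Screening PFS, baseline 2-AG and ghrelin, arm, BMI, baseline physical activity | Any on-treatment PFS |
| If she reached week 4: weight, dietary intake, tablet count | Any on-treatment 2-AG or ghrelin |

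**Step 4: precision gained from a week-4 PFS.** With a week-8 value for 39.1 women and a week-4 value for m women,

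effective n = 1 / [(1 − R²)/39.1 + R²/m].

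If every loss comes after week 4, m = 46. If only half do, m = 39.1 + 0.5 × 6.9 = 42.55.

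| r | R² | Effective n, all losses after week 4 | Effective n, half after week 4 |
|---|---|---|---|
| 0.5 | 0.25 | 40.6 | 39.9 |
| 0.7 | 0.49 | 42.2 | 40.7 |
| 0.8 | 0.64 | 43.3 | 41.2 |

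Worked example for r = 0.7 and m = 46: 0.51/39.1 + 0.49/46 = 0.01304 + 0.01065 = 0.02370, and 1/0.02370 = 42.2.

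**Step 5: in standard-error terms.** With all losses after week 4, the standard error is multiplied by √(39.1/40.6) = 0.98 at r = 0.5, √(39.1/42.2) = 0.96 at r = 0.7 and √(39.1/43.3) = 0.95 at r = 0.8: a fall of about 2% to 5%. The comparison ignores whatever week-4 weight, diet and tablet counts already contribute, so the true increment is somewhat smaller.

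**The case against.** Measuring at baseline and at the end of treatment is a normal design for an 8-week pilot whose main aim is to provide data for sizing a larger trial. The sections agree on the schedule, the comparison of interest is at week 8, the sample was already enlarged for attrition, and the weekly calls are meant to limit it. The gain in precision is small. All of this stands, and it is why the point is an improvement and not an error.

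Four stronger readings are tempting, and the document does not support them:

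- **That imputation has nothing to work with.** Step 3 shows otherwise. What is absent is an on-treatment value of the outcome itself.
- **That a woman who stops tablets leaves the trial.** Blinding says "If dropout rates reach 15% or higher due to adverse effects, we will conduct an intention-to-treat (ITT) analysis", which describes dropouts with a cause. It does not define every woman who stops tablets as a dropout. Intervention and Data management and monitoring tell women with attributed adverse events to discontinue the supplement; neither says that they miss the week-8 assessment. The protocol is silent on this, and a journal article may leave it to the full document.
- **That a week-4 PFS would reveal whether leavers responded differently by arm.** With 3 to 4 losses per arm, it could not do so reliably.
- **That the gap is repaired for all primary outcomes.** A questionnaire does nothing for 2-AG or ghrelin.

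**Conclusion.** The point holds as a cheap improvement of minor weight. The PFS is taken only at screening and at the end although a suitable visit lies between, and at the planned attrition about 7 of 46 women would have no on-treatment PFS.

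The gain in effective sample size is at most about 1.5 to 4 women (40.6 − 39.1 = 1.5; 43.3 − 39.1 = 4.2). That rests on assumed correlations of 0.5 to 0.8 and on all losses coming after week 4. If only half do, it is about 0.8 to 2.1 women, and for losses before week 4 the visit itself adds nothing. The stronger argument is that the missing-at-random assumption becomes more credible when an on-treatment PFS is in the imputation model. Whether women who stop tablets are assessed at week 8 is a matter for clarification only.

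**What to change.** 1. Give the PFS to every participant at the existing week-4 visit, and by the weekly call to anyone who leaves earlier.
2. Name the week-4 PFS as an auxiliary variable in the imputation model for week-8 PFS. Keep week 8 as the primary time point.
3. As a secondary clarification, state whether women who stop tablets are still assessed at week 8.

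The cost is one more administration of a 15-item questionnaire, with no new visit, blood draw or assay. The downside is an additional exposure to the questionnaire, equal in both arms. A by-product is an estimate of the within-woman correlation of the PFS over time, which serves the pilot's aim of informing the sample size of a larger trial.

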**Discussion:**

Considering the positive effects of melatonin supplementation in reducing endocannabinoid levels, the expression of the ghrelin hormone gene, the level of ghrelin, and the cannabinoid receptor type 1 gene expression in animal studies, it is possible that in human subjects, it could impact the intensity of hedonic eating by lowering endocannabinoid and ghrelin levels.

**Trial registration:**

The trial was registered with the Iranian Registry of Clinical Trials in June 2023 under the ID number IRCT20080904001197N22.

## Introduction

Appetite and food intake are complex functions that are partially controlled by two systems: the homeostatic system and the hedonic system. The homeostatic system responds to biological signals related to energy levels, such as depleted or replenished energy stores, while the hedonic system is associated with reward mechanisms related to dopamine. Especially palatable foods activate reward mechanisms, leading individuals to consume them repeatedly. Over time, these processes can contribute to weight gain and obesity [1].

In hedonic eating, palatable foods can activate the brain’s reward circuits by releasing dopamine. Additionally, these types of foods can lead to the release of endocannabinoids and opioids, which in turn may help increase the release of dopamine [2–4].

Endocannabinoids are a crucial component of the endocannabinoid system, which includes of cannabinoid receptors, such as cannabinoid receptor type 1 (CB1) and cannabinoid receptor type 2 (CB2), as well as their endogenous ligands, like 2-arachidonylglycerol (2-AG) and N-arachidonylethanolamine (AEA). This system plays an important role in regulating food intake and hedonic eating. In the limbic system, activation of CB1 receptors by endocannabinoids released during the eating of palatable foods can increase food intake especially hedonic eating by stimulating the release of dopamine [4–8]. Also, in addition to ghrelin’s role in the homeostatic regulation of food intake, previous studies have shown that ghrelin level rises rather than drop in response to the consumption of palatable foods under satiety conditions. It has been proposed that ghrelin plays a significant role in hedonic eating by stimulating the release of dopamine, increasing the activity of dopamine receptors, and affecting the opioid receptors involved in food reward [9–11]. In the study conducted by Monteleone et al., consuming food for pleasure increased the plasma levels of ghrelin and 2-AG, and the levels of these two substances showed a positive correlation [2].

In addition to biochemical parameters, such as endocannabinoids and ghrelin, the Power of Food Scale (PFS), designed in 2009 by Lowe et al., is routinely used to assess individual differences in hedonic eating intensity [12]. The PFS is a self-report instrument used to assess individual differences in thoughts, feelings, and motivations related to appetite in environments where palatable foods are available [13].

Due to the important role of hedonic eating in the development of overweight and obesity, weight management interventions targeting hedonic eating have been linked to greater weight loss [14–16]. Melatonin, a hormone secreted from the pineal gland, has several roles, including regulating sleep and circadian rhythm, promoting weight loss, and exhibiting antioxidant and anti-inflammatory properties [17–19]. Animal studies have shown positive effects of melatonin supplementation on reducing levels of endocannabinoids, ghrelin, and CB1 expression [7,20–24], suggesting it may also be effective in hedonic eating. To date, no published study has specifically investigated the effect of melatonin supplementation on hedonic eating. Therefore, this pilot study will investigate the effects of melatonin supplementation on plasma levels of 2-AG, ghrelin, and the intensity of hedonic eating in women who are overweight or obese and have high hedonic eating intensity.

### Hypothesis

We hypothesized that melatonin supplementation may improve hedonic eating intensity by affecting levels of endocannabinoid 2-AG, and ghrelin.

## Methods and design

### Study design

The present pilot study is a two-arm, parallel-group, randomized, double-blind, and placebo-controlled superiority clinical trial. The timeline and flowchart of the study are presented in Figs 1 and 2. This intervention will take place in the Nutrition Research Laboratory of the Faculty of Nutrition and Food Sciences at Tabriz University of Medical Sciences, Tabriz, Iran. Its purpose is to investigate the effects of melatonin supplementation on the plasma concentrations of 2-AG and ghrelin, as well as on the hedonic eating score, dietary intake, and body weight in women with overweight/obesity and high hedonic eating intensity. The trial’s protocol adheres to the recommendations for a clinical trial protocol (S1 Checklist, SPIRIT 2013 checklist).

**Fig 1 pone.0319258.g001:**
[figure not shown]
SPIRIT Schedule of enrolment, intervention, and assessments of the outcomes.

**Fig 2 pone.0319258.g002:**
[figure not shown]
Study protocol flowchart, adapted from CONSORT.

### Sample size

Currently, no human studies have investigated the use of melatonin supplementation on hedonic eating. The proposed study is a pilot project; its main aim is to establish data for sample size calculations for a larger trial. Various studies recommend a total sample size of at least 24 participants for a two-arm trial [25]. Considering the sample size of previous studies on melatonin supplementation in overweight and obese Iranian women [26,27] and to increase the accuracy and power of the study, in this clinical trial, we plan to enroll 40 participants, which, with a 15% attrition rate, will increase to 46 subjects (23 in each group).

### Study population

The present pilot study is the second phase of a Ph.D. dissertation. The first phase of the project is cross-sectional, and approximately 400 overweight or obese females (BMI: 25–34.9 kg/m²) will be recruited through advertisements in public places, social media, fitness centers, etc. The high hedonic eating intensity will be assessed using the PFS, which has previously been validated in the Persian population [28]. Forty-six volunteers who exceed the threshold score, meaning a total PFS score > 2.5 [29,30], will proceed to the next phase of the research, which involves intervention. All eligible participants will receive comprehensive information regarding the research procedures by the principal investigator, and consent will be obtained by signing an informed consent document (S1 File).

### Inclusion and exclusion criteria

For the current study, 46 adult women meeting the following inclusion criteria will be recruited: apparently healthy volunteers (individuals who have not been diagnosed with any medical conditions and are not taking any medications), literate, aged 19–49 years; BMI = 25–34.9 kg/m²; exhibiting high hedonic eating intensity (total PFS score > 2.5); and expressing a desire to use drugs or supplements for weight loss instead of dieting.

Participants will be excluded based on the following criteria: being postmenopausal, pregnant, or lactating; having irregular menstruation; recent weight loss or participation in weight loss programs; current smoking status; recent use of supplements affecting appetite or weight (within the last 3 months); substance abuse; alcohol consumption; any chronic diseases; use of appetite-affecting drugs (such as antidepressants, steroids, and oral contraceptives); working night shifts; severe insomnia [as determined by the Insomnia Severity Index (ISI)]; use of drugs that interfere with melatonin (such as anticonvulsant drugs, anticoagulant drugs, sedatives).

As mentioned, the present pilot study is the second phase of a Ph.D. dissertation. The project’s first phase is cross-sectional, and approximately 400 overweight or obese females will be recruited. The mentioned inclusion and exclusion criteria will be assessed in the first phase of the project.

